### Recruitment {15}

In all centers, physicians who participated in this trial were informed of the admittance criteria, and participants will be recruited mainly via physician referrals from the gastroenterology clinics. There are posters and leaflets designed for the recruitment delivering to all centers and placing inside the hospital and community. Those who are willing to participant in this trial will need to contact the investigator and research assistants by telephone.

## Assignment of interventions: allocation

### Sequence generation {16a}

According to the randomization scheme of clinical research, statistical experts randomly code experimental drugs. The experimental drugs are randomly encoded as the unique identifier of the subjects. The subjects and investigators must stay in blind state from the beginning to the end, and changes of schedule will be communicated by the independent staff during the period.

Using the SAS 9.4 statistical software PROC PLAN process to generate a random arrangement of the subjects (the *Bifidobacterium* quadruple viable tablet and placebo) which lists the random coding table, a block randomization model will be applied with a block size of 4.

### Concealment mechanism {16b}

The blinding work will be accomplished by the primary sponsor, principal investigator, and statisticians. Two-dimensional blinding will be conducted. The first dimensional blindness will be implemented for drugs applied in the trial that the *Bifidobacterium* quadruple viable tablet and placebo are in identical appearance and uniformly packaged, while the code of the experimental drug package will be set as the second dimensional blindness. Treatment allocations will be kept into envelops in confidence. One will be saved by staff member from the Clinical Drug Trial Institution, while the others will be sent to each center with drugs as the emergency envelop.

### Implementation {16c}

A statistician not involved in this trial will perform the sequence allocation and block randomization with a block size of 4. The drug number assigned to each center will be random. In this trial, 14 centers are proposed; each center is based on the setting rules, that is, led by the principal investigator and sorted by the initial Chinese phonetic alphabet.

## Assignment of interventions: blinding

### Who will be blinded {17a}

This double-blind controlled trial is designed blinded to the investigators, the subjects, and the outcome assessors.

### Procedure for unblinding if needed {17b}

The blinding will be maintained until serious adverse event occurs. Once blinding is broken, the trial will be aborted and the subject will be marked as a shedding case. The management result will be reported to the supervisor with specific reason, date, and sign recorded on CRF.

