#### Interim analyses {21b}

There will be no interim analysis. The study will continue until the 300 participants have completed the study since there were no anticipated problems that are detrimental to the participant.

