### Composition of the data monitoring committee, its role, and reporting structure {21a}

An independent data monitoring committee comprising experts in clinical epidemiology, statistical staff, gastroenterologist, and clinical research associates (CRAs) is established before the patient enrolment. The trial protocol is reviewed. The data monitoring committee will get a copy of all severe adverse event reports as soon as they become available to the trial investigators. The data monitoring committee will review the reports and report back to the investigators if any further action is required.

There will also be CRAs who are not taking part in this study appointed to be responsible for conducting systematic inspection and monitoring the trial according to the GCP principle, ensuring that the trial scheme is carried out according to the provisions and that the data recorded in the CRF are in accordance with the original data.

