### Adverse event reporting and harms {22}

Subjects will be instructed to report changes of their symptoms truthfully during the trial. Curative effects will be monitored, as well as adverse reactions and unexpected side effects. Adverse events must be recorded in detail whether they are related to the trial or not, including time of occurrence, clinical manifestations, severity, duration, results of laboratory tests, management and outcome, and follow-up times. History of medications is also significant to be on record to analyze causality between adverse events and experimental drugs. If any serious adverse event (SAE) occurs, it must be reported to the Province Food and Drug Administration, the State Food and Drug Administration, the primary sponsor institution, the research institutions, and the Ethics Committee within 24 h. Record shall be signed and dated by the researcher who reported the serious adverse event. The blinding will be maintained until SAE occurs. Once blinding is broken, the trial will be aborted and the subject will be marked as a shedding case. The management result will be reported to the supervisor with specific reason, date, and sign recorded on CRF.

When any AE occurs, clinician shall evaluate subject’s condition and provide suitable intervention or treatment. If any SAE occurs, the research institution must take necessary measures to keep subject out of health-threatening danger and stay follow-up until subjects have been resolved.

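### The unblinding rule makes any serious adverse event end the blind and abort the trial, contradicting the protocol's blinding, continuation and monitoring rules and leaving the scoring of that participant unsettled

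*Protocol article*

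**What the plan says.** All references are to the protocol article.

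- **Trigger.** Procedure for unblinding if needed {17b}: "The blinding will be maintained until serious adverse event occurs". Adverse event reporting and harms {22} says the same: "The blinding will be maintained until SAE occurs". Neither section limits this to related events, to cases where care depends on knowing the treatment, or to a decision by a named role.
- **Consequence.** Both sections continue: "Once blinding is broken, the trial will be aborted and the subject will be marked as a shedding case". The reason, date and signature then go on the case report form.
- **General blinding rule.** Sequence generation {16a}: "The subjects and investigators must stay in blind state from the beginning to the end".
- **Emergency codes.** Concealment mechanism {16b} keeps one set of allocation envelopes centrally, "while the others will be sent to each center with drugs as the emergency envelop".
- **Continuation.** Interim analyses {21b}: "The study will continue until the 300 participants have completed the study".
- **Oversight.** The data monitoring committee section {21a} sends all SAE reports to the committee: "The data monitoring committee will review the reports and report back to the investigators if any further action is required".
- **After an SAE.** Section {22} also requires the institution to "stay follow-up until subjects have been resolved".
- **Scoring.** Under Participant request, in the discontinuation criteria {11b}, a subject who asks to leave is a shedding case, recorded as a treatment failure. Sections {20b} and {20c} fill missing data in the full analysis set (FAS) by last observation carried forward (LOCF).

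**The concern.** Section {17b} is where the protocol fixes its unblinding procedure, so this is a stated rule and not detail left to another document. It ties the end of the blind to the SAE itself. Fourteen centres have to apply that text, and three things follow if they do.

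1. The code is opened for every SAE, including events unrelated to the tablets or manageable without knowing the allocation.
2. Nothing ensures that causality is judged before the allocation is known. Section {22} asks for medication history to support that judgement, and the Discussion presents safety assessment as a gap the trial is meant to fill.
3. A shed subject's diary probably stops, so efficacy data end because of an event after randomisation. The endpoint is built from subjective daily scores, and the article does not say how the rest of that subject's treatment period is scored.

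**Working it through.** **Step 1. The rules side by side.**

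| Section | Rule | Compatible with {17b}/{22} as worded? |
|---|---|---|
| {16a} | Subjects and investigators blind throughout, no exception | No: an SAE ends the blind |
| {16b} | Emergency envelopes at each centre | Points to case-by-case code breaks, which {17b} does not describe |
| {21b} | Study runs until 300 have completed | No, if "Once blinding is broken, the trial will be aborted and the subject will be marked as a shedding case" is taken at its word |
| {21a} | Committee reviews SAE reports and advises on action | No: this presupposes that the trial goes on after an SAE |
| {22} | Follow-up to resolution | Yes: safety follow-up can continue for a shed subject |

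The conflicts are with {16a}, {21b} and {21a}. The follow-up sentence in {22} is at most a tension.

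**Step 2. Scoring of an unblinded subject.** Take a participant who meets both the pain and the stool criteria in week 1 and has an SAE with a code break at the start of week 2.

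- If a shedding case is a treatment failure ({11b}), the participant is a non-responder.
- If LOCF applies ({20b}, {20c}), and assuming that the weekly status is what is carried forward, weeks 2 to 4 copy week 1. The participant then has 4 of 4 improved weeks and is a responder.

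The same data give opposite results. Section {11b} states the failure rule only for participant-request withdrawals, and {17b} does not say which rule governs a code break.

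**Step 3. The plan's sample size, reproduced.** Inputs from Sample size {14}: 50% v 30%, α = 0.05, power 90%. Two-sided testing is from {20a}. With pooled variance and no continuity correction:

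n = [1.960·√(2·0.4·0.6) + 1.282·√(0.5·0.5 + 0.3·0.7)]² / 0.2² = 124 per arm.

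This matches the stated 124. The allowance is 300 − 2·124 = 52 subjects, or 52/300 = 17.3%. Power is 90.0% at 124 per arm and 94.6% at 150 per arm.

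**Step 4. Size of the effect.** The article gives no SAE rate, so a rate p is assumed. Expected subjects affected = 300·p. Power starts from 150 per arm, with the same rate in both arms. Excluding the subjects gives 150·(1 − p) per arm. Counting them as failures multiplies both response rates by (1 − p).

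| Assumed p | Subjects affected | Power if excluded | Power if counted as failures |
|---|---|---|---|
| 0.5% | 1.5 | 0.9452 | 0.9445 |
| 1% | 3 | 0.9442 | 0.9428 |
| 2% | 6 | 0.9422 | 0.9392 |
| 5% (stress case) | 15 | 0.9355 | 0.9276 |

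Every row is well inside the allowance of 52, and power stays above the planned 90%.

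**The case against.** The best defence is that the text is clumsy and the intention clear. The heading of {17b} says unblinding happens if needed. The sentence about aborting goes on to speak of one subject, and the next concerns that subject's case report form. Emergency envelopes at each centre are the usual tool for single code breaks. The general rule in {16a} can be read as the default, with {17b} as its exception. Sections {21a} and {21b} show that nobody expected the study to stop.

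Much of this stands, and it rules out several stronger readings that a reader might infer:

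- **That one SAE ends the whole trial.** At assumed rates of 0.5%, 1% and 2%, the chance of at least one SAE in 300 is 1 − (1 − p)^300 = 78%, 95% and 99.8%. A rule so likely to stop the study could hardly sit beside {21b}. The trial most plausibly means that subject's participation, so these figures do not measure a real risk.
- **That these subjects' outcome data are removed.** No section takes a shedding case out of the FAS. Section {18b} records the latest outcomes at withdrawal, and {11b} keeps case report forms for analysis, although it does so under participant-request withdrawal. The likely loss is of later diary data.
- **That causality is judged after the code is open.** The article sets no order. It only fails to protect a blind judgement.
- **That each code break reveals something about the other three subjects in a block of 4.** This requires site staff to know the block size and block membership. The article does not say that they do, and {16c} gives the sequence to a statistician outside the trial.

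The defence does not remove the core point. The trigger is unconditional and written twice, neither place limits the consequence to the participant, and the scoring rule remains open.

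**Conclusion.** The point holds as a contradiction in the wording of a stated rule, with a real but small effect. Sections {17b} and {22} cannot be followed as written together with {16a}, {21b} and {21a}. Following them would open the code for every SAE regardless of need, leave blind causality assessment unprotected, and probably end efficacy data for those subjects, whose scoring is undefined between {11b} and {20b}/{20c}.

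About 1.5 to 6 of 300 subjects would be affected at an assumed SAE rate of 0.5% to 2%; the rate is an assumption, not a figure from the article. Neither the sample size nor the power is in question. What is at stake is the integrity of the blind and of the safety assessment, together with an unambiguous endpoint for a handful of participants. The documents do not support reading this as a rule that stops the trial at the first SAE or deletes participants from the analysis. The correction should be made because it is cheap and every centre depends on the text.

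**What to change.** 1. Reconcile {16a}, {16b}, {17b}, {21a}, {21b} and {22} into one participant-level unblinding rule. An SAE report should not by itself open the code, and the sentence about aborting should refer to that participant only. The existing requirement to record reason, date and signature can stay.
2. State that an unblinded participant remains in the FAS in the assigned arm, with diary and safety data still collected where possible.
3. Reconcile the treatment-failure rule in {11b} with LOCF in {20b} and {20c}, so that one scoring rule covers participants unblinded after an SAE.

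Whether study treatment stops after an SAE or a code break is a clinical matter. The sponsor needs to reconcile the sections on it, and no rule is proposed here.

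The cost is protocol wording, a line in the analysis plan, and the approval that {25} requires for any amendment. It needs no additional patients. Continued diary collection uses the log participants already keep.

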## Data collection and management

### Plans for assessment and collection of outcomes {18a}

A training regarding the trial-related procedure will be conducted by the principal investigator for all staff members participating before the implementation of the trial.

In the screening period, data of following contents will be collected:
General information including demographic characteristics (gender, age) and previous and present medical history.Scores of Hamilton Anxiety and Depression Rating Scales (HAMA and HAMD) investigated by the trained raters.Physical examination (general and abdominal) and vital signs including temperature, heart rate, respiratory rate, and blood pressure.Laboratory tests including blood routine, urine routine, stool routine, and occult blood test; fasting blood glucose; tests of liver and kidney function; and electrocardiogram.Abdominal ultrasonography and colorectal colonoscopy. Urine pregnancy test only in women of childbearing age.Complete the symptom log everyday including the strength of abdominal pain, fecal traits, level of overall symptom relief, patterns of defecation, remedial medication, and any other drug history permitted in this trial.Adverse events and concomitant medication.

Patients who are admitted in the trial will be allocated randomly into two groups in a ratio of 1:1, heading to the double-blind treatment period.

In the baseline period, investigator shall give subjects physical exam again and subjects will be required to complete the IBS-QOL (quality of life) scale. Data will be recorded in CRF. Feces will be collected to study the microbiome and metabolome at this period.

In the follow-up period, subjects shall update HAMA, HAMD, and IBS-QOL again, and insist to complete the symptom log and records of concomitant drugs and adverse events every day. Researchers shall perform physical exam and record the results and vital signs as same as previous times.

### Plans to promote participant retention and complete follow-up {18b}

Before every follow-up, investigators will make a phone call to patients to ensure if they are ready for the visit. Patients will also be able to contact investigators through the same method when they are confused or in emergency. Once there are patients withdrawing from the trial, the reasons for withdrawal shall be recorded as soon as possible as well as all of the latest outcomes.

### Data management {19}

In this trial, we designed the paper CRF and built the EDC system (Electronic Data Capture System) according to the paper CRF. The investigators were responsible for collecting information from each of the subjects every follow-up, inputting to the EDC system and data reduction. The data will be entered by the investigators or authorized persons (such as CRC), and the data manager will use the EDC system for data management. eCRF will be provided for researchers and authorized persons to record the data.

### Confidentiality {27}

The data manager is responsible for establishing the database which will only open access to investigator and supervisor to keep data and information confidentially. Database will be locked after the blind data verification report and statistical plan are finished; data will not be permitted to be modified anymore.

### Plans for collection, laboratory evaluation, and storage of biological specimens for genetic or molecular analysis in this trial/future use {33}

Stool samples of subjects will be collected at baseline (week 0) and the end of treatment period (week 4). Macrogenomics and metabonomics will be tested to analyze the efficacy of the intervention to the microbiota. Further analysis including the differences between responders and non-responders will be performed.

## Statistical methods

### Statistical methods for primary and secondary outcomes {20a}

#### General analysis

Statistical analysis will be performed by using the SAS 9.4 (or updated version) software (SAS Institute Inc., Cary, NC, USA). In terms of data description, quantitative data will be presented as mean ± standard deviation, median, minimum, maximum, lower quartile (Q1), and upper quartile (Q3), respectively. The categorical data will be presented as frequency and percentage. The comparison of the two groups will be analyzed in proper methods according to the type of indicators. The quantitative data from the two groups will be compared on the basis of data distribution (variance homogeneity, normal distribution) using group *t* test or Wilcoxon’s rank-sum test. A chi-square test or Fisher’s exact test (if the chi-square test is not applicable) will be applied on the categorical data, and Wilcoxon’s rank-sum test or CMH-*χ*^2^ test for the ranked data. Two-sided tests will be applied in all statistical tests, and a *P* value equal to or less than 0.05 will be considered statistically significant (except for special instructions).

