**Methods/design:**

A multicenter randomized controlled trial will be performed in fourteen hospitals. A total of three hundred patients who fulfill the eligibility criteria will be stratified divided into an experimental group and a control group randomly in a ratio of 1:1. The experimental group is treated with the *Bifidobacterium* quadruple viable tablet while the control group is treated with placebo. All the patients will receive a 4-week treatment and a 2-week follow-up. The primary outcome is the effectiveness in improving abdominal pain and stool consistency; the secondary outcome includes evaluation of overall symptom relief, frequency of defecation, bloating, urgency of defecation, remedial medication, score of IBS-QOL, and changes of microbiota and metabonomics. Physical examination, vital signs, laboratory tests, adverse events, and concomitant medication will be taken into account for intervention safety assessment during the trial.

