#### Intervention description {11a}

Subjects of two groups will receive three tablets of either the *Bifidobacterium* quadruple viable tablet or the matched placebo three times a day at 30 min after breakfast, lunch, and dinner, respectively, for consecutive 4 weeks. During the treatment period, researchers will give subjects physical exams and record the results as well as vital signs. Subjects are supposed to keep completing the symptom log every day and record remedial medication and any other drug history permitted in this trial. HAMA, HAMD, IBS-QOL, and laboratory tests will be updated at the end of treatment period.

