### Outcomes {12}

#### Primary outcome measures

The primary outcome of this trial is the response rate. A patient is categorized as a responder if the patient is a responder in both pain intensity and stool consistency. The strength of abdominal pain will be evaluated by numerical rating scale using 0 to 10 to represent different levels of pain: 0 means no pain and 10 means severe pain (unable to perform activities of daily living). The consistency of stool will be assessed by using the Bristol Stool Form Scale (BSFS), classified into seven categories:
Type 1: Separate hard lumps, like nuts (hard to pass)Type 2: Sausage-shaped, but lumpyType 3: Like a sausage but with cracks on its surfaceType 4: Like a sausage or snake, smooth and softType 5: Soft blobs with clear cut edges (easy to pass)Type 6: Fluffy pieces with ragged edges, a mushy stoolType 7: Watery, no solid pieces, entirely liquid

The treatment will be considered effective when two criteria are reached simultaneously.

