##### Quality of life

Subjects will be asked to finish IBS-QOL scale at baseline (week 0), the end of treatment period (week 4), and follow-up period (week 6) successively.

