### Sample size {14}

Sample size calculation was performed by using PASS 13. The 4-week treatment effective rate would be adopted as the main evaluation indicator. According to the systematic review published by Zhang et al. [23], when overall symptom relief is regarded as the main evaluation indicator, the effective rate of probiotics was 50% while placebo was 30% in IBS-intervened RCTs. On this basis and combined with clinical experience, it was assumed that the 4-week treatment effective rate of the experimental group was 50% and that of the placebo group was 30%. In the case of *α* = 0.05 and the power of test was 90% (*β* = 0.10), the required sample size would be at least 124 pairs. Considering the certain shedding and withdrawal samples (52 patients), the planned sample size would be 150 cases/group, and the total would be 300 cases (into a 1:1 ratio).

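### IBS-QOL is to be compared by an unadjusted t test or rank-sum test chosen on the data's distribution; ANCOVA on the baseline score already collected would be more precise

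*Protocol article*

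**What the plan says.** The General analysis section, under the heading for primary and secondary outcomes {20a}, sets one rule for all quantitative data: "The quantitative data from the two groups will be compared on the basis of data distribution (variance homogeneity, normal distribution", and the comparison is then made "using group *t* test or Wilcoxon’s rank-sum test". It adds that "Two-sided tests will be applied in all statistical tests". No section of the article names an analysis of covariance, a mixed model or any baseline covariate.

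The outcome this mainly concerns is IBS-QOL. Under Quality of life, subjects are to "finish IBS-QOL scale at baseline (week 0), the end of treatment period (week 4), and follow-up period (week 6"). The abstract lists the secondary outcome as "score of IBS-QOL, and changes of microbiota and metabonomics", where the word for change is attached to the stool measures and not to IBS-QOL. No section defines the IBS-QOL endpoint further.

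Two other scales are repeated. The Intervention description says "HAMA, HAMD, IBS-QOL, and laboratory tests will be updated at the end of treatment period", and the data collection section has HAMA and HAMD at screening and again in follow-up. Neither appears under Secondary outcome measures.

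The primary outcome is of a different kind: "The primary outcome of this trial is the response rate", a yes/no result already defined against the pre-treatment period.

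**The concern.** Two features of the rule are weak for a scale that is measured before and after treatment.

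First, neither test adjusts for the baseline score. Patients who start with a poor quality of life tend to end with a poorer one. A comparison that does not model this leaves explainable variation in the error term. The baseline has been collected, so the precision is there to be had.

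Second, the choice of test depends on how the data are distributed. A t test addresses a difference in means and a rank-sum test addresses a shift in ranks. Until the data are seen, it is not settled which quantity the trial will report for IBS-QOL. With 124 to 150 patients per group, a comparison of means does not depend on normal data for its validity, so little is gained by leaving the choice open.

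At stake are the width of the confidence interval and the power for a secondary outcome, and having one effect measure fixed in advance.

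**Working it through.** **The plan's own figure.** The Sample size section assumes response rates of 50% and 30%, with alpha "0.05 and the power of test was 90"%. With pooled variance, two-sided and no continuity correction:

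n = [1.960 × √(2 × 0.4 × 0.6) + 1.282 × √(0.5 × 0.5 + 0.3 × 0.7)]² / 0.2² = 124 per group.

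This matches the stated 124. The allowance of 52 patients is 300 − 2 × 124, or 52/300 = 17.3%. These figures concern the binary primary outcome and stand. The article gives no power calculation for IBS-QOL.

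**Inputs for IBS-QOL.** The number per group is taken as 124 (Sample size section). The protocol gives no standard deviation, effect size or baseline to follow-up correlation r. I assume equal standard deviations at baseline and follow-up, a linear relation with the same slope in both groups, and r = 0.3, 0.5 or 0.7.

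**Variance of the group difference**, relative to an unadjusted test of the post-treatment score:

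- ANCOVA: 1 − r²
- Change score: 2(1 − r)
- ANCOVA relative to change score: (1 − r²) / [2(1 − r)] = (1 + r)/2

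| r | ANCOVA / post score | Change score / post score | ANCOVA / change score |
|---|---|---|---|
| 0.3 | 0.91 | 1.40 | 0.65 |
| 0.5 | 0.75 | 1.00 | 0.75 |
| 0.7 | 0.51 | 0.60 | 0.85 |

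ANCOVA has the smallest variance in every row. Below r = 0.5 the change score is less precise than the post-treatment score alone.

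**In patients.** To match the precision of the post-score test with 124 per group, ANCOVA needs 124 × (1 − r²): 113, 93 and 64 per group at r = 0.3, 0.5 and 0.7.

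**In power.** As a reference I take the effect that the post-score test with 124 per group detects with 80% power: (1.960 + 0.842) × √(2/124) = 0.356 SD. This effect is also an assumption.

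| r | Post-score t test | Change-score t test | ANCOVA |
|---|---|---|---|
| 0.3 | 80% | 65.8% | 83.6% |
| 0.5 | 80% | 80.0% | 89.9% |
| 0.7 | 80% | 95.1% | 97.5% |

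A simulation with normal data (4000 trials per value of r) agrees. At r = 0.5 the simulated power was 0.79 for both t tests, 0.77 for the rank-sum test on the post-treatment score and 0.89 for ANCOVA. At r = 0.3 ANCOVA was again highest, at 0.83.

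**The case against.** The strongest reply is that nothing here is an error. In a randomised trial the unadjusted test is unbiased, and its type I error already allows for chance imbalance at baseline. The trial was not powered on IBS-QOL. This stands: the loss is of precision only, and on a secondary outcome.

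A second reply is that this is a condensed article. The section speaks of choosing suitable methods by type of indicator, and the Confidentiality section refers to a statistical plan to be finished before the database is locked. Covariates and the main time point often belong there. This stands in part. However, the article does not leave the method open. It names the tests, and a plan that follows it would carry the weakness over.

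Three stronger readings are tempting, and the documents do not support them:

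- **That the baseline is thrown away.** The article does not say whether the score or the change is tested. The abstract's wording points towards the score, but it is a label and not an endpoint definition. A t test on change fits the text and uses the baseline. It is still less precise than ANCOVA for any r below 1.
- **That formal tests of normality will pick the method.** The text says the choice rests on the distribution and names no pre-test. A choice made during blind review would weaken the objection to a data-dependent choice, but the article does not say when it is made.
- **That HAMA and HAMD are affected secondary outcomes.** They serve as eligibility thresholds and are collected again, but they are not in the list of secondary outcomes. The Discussion mentions psychological status only in general terms.

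The last-observation-carried-forward rule is a separate matter, and this point does not depend on it.

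**Conclusion.** The point holds as a precision gain on IBS-QOL that needs no new data. As written, the comparison is an unadjusted two-group test whose form depends on the data's distribution, while the baseline score is available. Against a post-score test, ANCOVA would cut the variance by 9% at r = 0.3, 25% at r = 0.5 and 49% at r = 0.7. Against a change-score test the cut would be 35%, 25% and 15%.

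The size rests on an assumed r, and the power figures also on an assumed effect of 0.356 SD. At the low end of the range the gain over a post-score test is small (80% to 83.6%). The direction does not depend on these choices for any r above 0 and below 1, given equal standard deviations.

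A reader might infer that the IBS-QOL result would be biased, or that the trial's main conclusion is at risk. Neither follows. Randomisation protects the unadjusted comparison, and the primary responder rate with its 124 per group is untouched.

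**What to change.** For IBS-QOL, prespecify the following before the database is locked and the blind is broken:

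- Use ANCOVA of the follow-up score on treatment with the week 0 score as covariate, or one repeated-measures model over weeks 4 and 6 with the week 0 score as covariate.
- Name week 4 as the main time point.
- Report the adjusted mean difference with its 95% CI.
- Keep the rank-sum test as a sensitivity analysis, and drop the choice of main test by distribution.
- If the repeated-measures model is used, state how it fits with the carry-forward rule in the missing-data section.

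Apply the same to HAMA and HAMD only if they are to be analysed as outcomes.

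The cost is a few sentences in the statistical methods section or the statistical plan. No further visits, data or patients are needed, because every score is already on the schedule.
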